# Protocol for a phase III wait-listed cluster randomised controlled trial of an intervention for mental well-being through enhancing mental health literacy and improving work friendliness in Hong Kong

**DOI:** 10.1186/s13063-019-3748-y

**Published:** 2019-12-04

**Keywords:** Mental health literacy, Work stress, Burnout, Health-related quality of life, Mental well-being, Workplace intervention, Psychoeducation, Work environment, Mental health promotion, Mental public health, e-Health

## Abstract

**Background:**

Mental health has long been recognised as a major global health issue. Some work-related characteristics have been identified to be associated with common mental health problems, and thus the workplace is an important venue for the prevention of mental health problems and promoting mental wellness. Burnout is one of the important aspects of workplace organisational stressors and, in recent years, the lack of mental health literacy has also been identified as a fundamental issue. Studies have demonstrated that an improvement in mental health literacy is an effective measure for enhancing mental well-being. It would be prudent to combine an organisation-directed component and the enhancement of mental health literacy in an intervention programme. This trial will examine the novel approach of an intervention aiming to provide an evidence-based prevention programme.

**Methods:**

This study utilised a wait-listed cluster randomised control trial design. Using branch offices as the primary sampling units, employees from three large companies in different industries will be recruited. Upon enrolment and after the baseline assessment of the outcome measures, participants nested in the branch offices will be allocated to the intervention or wait-listed arms. The intervention programme comprises of two main elements: an organisation-directed component and individual-directed psychoeducation training. This intervention will be delivered by a senior social worker well-versed in workplace issues over a period of 3 months. The trial will determine whether an integrated workplace mental health literacy and well-being programme is effective in increasing the mental health literacy scores and reducing burnout and stress scores, as measured by standardised and validated scales.

**Discussion:**

If the trial results are in line with the hypothesis that supports the efficacy of the intervention programme, this will provide an evidence-based approach for an effective workplace mental well-being intervention programme that could not only enhance the understanding of mental health issues, but also reduce work-related burnout and stress as well as increase workers’ quality of life.

**Trial registration:**

Australian New Zealand Clinical Trials Registry (ANZCTR), ACTRN12619000464167. Registered prospectively on 20 March 2019.

## Background

Mental health has long been identified as a major global health issue. Mental and substance disorders are the leading cause of years lost due to disability (YLD), accounting for about 21.2% of the global burden of diseases [1]. A recent study with more precise calculations has revised the burden to 32.4%, rendering mental illnesses the top cause of YLD [2]. In Hong Kong, while information on the overall mental health status has been scarce, results obtained from the Hong Kong Mental Morbidity Survey (HKMMS) suggested that common mental disorders were the most prevalent [3]. The point prevalence of mixed anxiety and depression disorders was estimated to be 13.3% in the adult population aged between 16 and 75 years [3]. Among these, only slightly more than a quarter (26%) sought help from mental health services and fewer than 10% consulted a general practitioner [3]. The latest Mental Health Review Report revealed that, based on the international prevalence of mental disorders and extrapolation, there could be as many as 1.1–1.8 million individuals experiencing a mental disorder in the adult population [4].

It has been estimated that, on average, full-time workers in the Organisation for Economic Co-operation and Development (OECD) countries spent about 38% of time in a normal day working (www.oecdbetterlifeindex.org/topics/work-life-balance/). While work is an essential part of our life and brings many benefits, some work-related characteristics have been identified to be associated with common mental health problems [5]. In a recent large-scale study on the mental and physical health of a working population, Rose et al. [6] found that work-related stress and fatigue were associated with mental health problems such as depression. While there has not been a wealth of studies on the mental health status in the workplace in Hong Kong, some other studies on specific topics have shed light on the issue of poor mental health and its effect on working individuals. A psychological autopsy conducted by Law et al. [7] found that, in a comparative study of 63 employees who committed suicide and 112 controls, psychiatric illnesses played an important mediating role in the association between chronic work-related stress and suicide. This suggested a potentially causal pathway between work-related stresses, mental ill health, and, subsequently, suicide [7]. In another recent study on suicide ideation and attempts among nurses in Hong Kong, it was found that about 15% had contemplated suicide and about 3% actually attempted suicide once or more in the year prior to the survey [8].

Mental health in the workplace has long been an important health concern internationally. The workplace has also been identified as an important venue for the prevention of mental health problems and for promoting mental wellness [9]. This, in fact, is also a main focus of the World Health Organization (WHO) comprehensive mental health action plan 2013–2020. The plan stated the paramount importance of prevention of and early intervention in mental health problems in the community, including the workplace [10]. Hence, improving mental wellness of the working population should be considered an important primary preventive strategy. Within the working context, this can be achieved through an early intervention programme designed specifically for employees in the workplace.

Many workplace intervention programmes have been developed in the past, with the majority mainly focused on one important aspect of work-related stressors, namely burnout [10]. A review study on the effectiveness of various intervention programmes in reducing burnout found that there were two main types of intervention programmes: person-directed and organisation-directed programmes [11]. Results of the review indicated that person-directed intervention programmes tended to be effective for a short term of 6 months or less, whereas intervention programmes directing at the organisation level achieved a longer-term effect of 12 months or beyond. As a result, it was suggested that any workplace intervention programmes should be designed with dual foci directed at both the organisation and individuals.

While acknowledging that burnout is an important aspect of workplace stress, it is only one of many pieces of the puzzle. In addressing the issue of mental health problems and to advance mental wellness in the community, attention has been drawn to a more fundamental issue, namely the lack of mental health literacy (MHL). MHL is a concept developed by Jorm et al. [12] about two decades ago. MHL has been defined as “knowledge and beliefs about mental disorders which aid their recognition, management or prevention” [12]. Since then the concept as well as the assessment methodology have been widely adopted. It has been argued that lack of understanding and awareness of mental health problems, compounded with self-and-other stigmatisation of these problems, were major barriers in help-seeking for people in need [13]. The reluctance and inaction in help-seeking resulted in the individual not receiving the appropriate and timely mental health assistance and, in turn, might exacerbate the condition [13]. In order to tackle the root of mental health problems, improving MHL was suggested to be an effective strategy for enhancing self-help-seeking behaviour or assisting others to seek help [13]. This in turn, might result in early diagnosis and treatment, and thus lighten the burden of mental illnesses in the population.

To determine the effectiveness of the approach in addressing the issue, a systematic review and meta-analytical study on the effect of intervention programmes, mainly on help-seeking behaviour, was conducted [14]. The results of the study revealed that interventions on enhancing mental health literacy were shown to be effective in increasing help-seeking attitude with an effect size ranging from 0.12 to 0.53 [14], although the effects on the actual help-seeking behaviour were not certain. On the other hand, a study on the relationship between mental health literacy and depression among young people indicated a significant association between the two. Young people who had experienced moderate to severe levels of depression were more likely to have an inadequate level of mental health literacy (OR = 1.52, 95% CI = 1.01–2.31) [15]. These results suggested that intervention programmes aiming to enhance the mental health literacy of individuals could have a positive effect on their actual mental health status, probably through an increased awareness of the problem, and also strengthened attitudes towards seeking appropriate help.

Given the aforementioned evidence from studies on burnout, it would be prudent to consider combining an organisation-directed component and the enhancement of mental health literacy in an intervention programme. In doing so, the creation of a positive environment can lead to greater efficacy in reduction of mental health problems and enhancement of mental wellness. Such an approach has not received much attention in the area of early intervention and prevention of mental health problems in the workplace. The study team has developed a novel approach to intervention taking into consideration the influential factors in workplace mental well-being. The proposed trial aims to submit this intervention to a proper scientific investigation for proven evidence on its efficacy.

The trial protocol reported here adheres to the Standard Protocol Items: Recommendations for Interventional Trials (SPIRIT) Checklist (see Additional file 1).

## Objectives

### Primary objective

The primary aim of the proposed study is to determine whether a workplace mental well-being intervention programme that responds to organisation and individual mental health needs, based on the dual approach of an organisation environment scan and evidence-based psychoeducation training in mental health literacy, would increase MHL.

### Secondary objectives

The study further aimed to investigate whether the intervention:
Reduces work-related burnout in workersIncreases the mental health well-being, particularly in the reduction of stress, of workersIncreases the general health-related quality of life of workers

## Trial design

The study will use a phase III wait-listed cluster randomised control trial (RCT) design with different work sites or branch offices as the primary units of randomisation (refer to Fig. 1).

**Fig. 1 Fig1:**
[figure not shown]
Study flow chart

## Methods: participants, interventions and outcomes

### Study setting

The study will focus on specific industries with a considerable level of work-related stress, such as the servicing and hospitality industries. Employees in these industries may have a large volume of customer or client interaction, or the job nature may carry heavy personal and/or interpersonal responsibilities. Currently, three large companies in Hong Kong have indicated willingness to be involved in the study. These include a company providing travel services, a real-estate company, and a property management company. All three companies have signed an agreement to willingly participate in the project.

### Eligibility criteria

#### Sites

Managers of the participating sites are willing to commit to the project and allow the study to be conducted at their branch offices.

#### Participants

All staff members working at the selected sites are eligible to participate in the study. However, participants have to indicate their willingness to participate in the study and to comply with the requirements of the study by signing the consent form.

### Exclusion criteria

#### Sites

Managers of any sites who are not willing to comply with the requirements of the study and not willing to allow the project team to conduct the workplace environment scan in the branch office will be excluded. Participants who are receiving training on workplace mental health will not be included in the study.

#### Participants

Any staff member at any site who has already received a similar psychoeducation training programme or has been involved in any similar intervention programme before will be excluded from the current intervention programme.

### Intervention

#### Intervention to be tested

The intervention programme comprises two main elements: an *organisation-directed* component and *individual-directed* psychoeducation training.

For the organisation-directed component, a workplace environment scan, using a standard protocol and the Moos Work Environment Scale (WES) [16], will be conducted by a senior social worker with expertise in workplace issues. The scan will take place at the commencement of the intervention programme prior to the individual-directed component. Different dimensions of the work environment, including workload (work pressure and task requirements), personal growth (professional growth, support, achievement value, and growth), conflict, and management relationships, will be assessed to gain a better understanding of the workplace issues at different sites. Information will be gathered via a staff survey and face-to-face interviews. De-identified and aggregated information collected from the assessment will be provided to the management of each participating site with professional interpretation of the findings. Possible strategies to resolve the identified issues will also be offered. Site management is encouraged to make use of this information to improve the work environment during the intervention and the follow-up period. Each site is encouraged to document changes in organisational practices and to, quantitatively and qualitatively, record any changes in the workplace in terms of morale, work performance, productivity, sick leave, and resignations. Information on these changes will be collated at the end of the project through interviews with site managers.

For the individual-directed component, participating sites will adopt the well-studied and evidence-based Workplace Mental Health First Aid (MHFA) training programme [17] with the inclusion of a module on stress reduction and burnout prevention. Based on the e-Health and e-Learning approach, this is blended training consisting of a series of self-paced online e-Learning modules. Participants will have access to these online modules to complete each at their own convenience. Upon completion of the online modules, a face-to-face group session lasting for about half a day will be conducted. The aim of the group session is to provide an opportunity for participants to clarify any queries interactively with the programme trainer and to gain hands-on experience through communication skills practices.

Pilot testing involved a small-scale pilot study conducted by the team on a mental health education and training programme in a sample of high school teachers and nurses in China. This project was set up as a joint initiative between the Australian and Chinese governments through the Australia China Council (ACC) of the Department of Foreign Affairs and Trades, Australian Government (http://dfat.gov.au/people-to-people/foundations-councils-institutes/australia-china-council/grants/grantees/Pages/mental-health-education-for-education-and-health-professionals-in-china.aspx). Although the focus of this project was not on workplace mental health, valuable lessons were learned in terms of cooperation between partners as well as the responses of young professionals towards a mental health education programme. These will inform the development of the current proposed study.

#### Pre-randomisation process

An operational agreement between the project and the site management will be established with the manager signing the consent form. Upon recruitment of participants, a briefing session will be conducted by a qualified senior social worker, trained in workplace psychosocial issues, with the manager of the site and the workers separately prior to the randomisation. The aim of the briefing is to provide details on the study and to obtain informed consent before the baseline assessment is conducted on the workers. During the session, the details and requirements of the study will be explained, and questions and concerns raised will be answered. This will be followed by administration of the baseline assessment (T0).

#### Intervention arm

Consenting participants nested in the sites that are randomised to the intervention arm will receive the intervention immediately (Fig. 1). The intervention will commence with a workplace environment scan. Results of the scan will be fed back to the manager of the site during a professional consultation session. The psychoeducation training programme will be implemented with all willing participants enrolled into the online modules and commencing the MHFA programme. Upon completion of the online modules by all participants at each site, a face-to-face session will be conducted on site at the workplace. At the end of the intervention programme, participants will then be re-assessed on the outcome measures (T1). The sites and participants in the intervention arm will be followed for another 3 months, with re-assessment conducted post follow-up (T2).

#### Control group

Consenting participants randomised to the wait-listed control group will also complete the baseline data collection measures, as those in the intervention group, but will not have access to the training programme until participants in the intervention arm have completed the programme with the re-assessment of the outcome measures. It is anticipated that the intervention programme will be implemented in the control group within 3–4 months after the commencement of the programme in the intervention arm. The same procedures will be applied to the controls as in the intervention arm, with re-assessment of outcome measures, immediately prior to the intervention (T1), at the end of the intervention (T2), as well as at the follow-up re-assessment (T3).

#### Adherence to intervention

Intervention adherence will be monitored weekly via record checking by the Research Assistant. Upon completion of one unit of online training, the participant will be informed automatically by the online platform to commence the next unit of the programme. For participants who are not progressing through the programme as planned, a short reminder message will be sent via common instant messaging applications, such as WhatsApp or WeChat. Should the participants encounter any problems or technical issues with the online programme, assistance will be provided by the project team through a hotline.

### Outcomes

#### Primary outcome measure

The primary outcome measure is the MHL of workers. MHL will be assessed using the Australian National Mental Health Literacy and Stigma Survey designed by Jorm et al. [12]. The instrument has been validated and widely used in many studies and different countries. As part of the international Mental Health First Aid collaboration, the MHAHK has permission from the Australian headquarters to translate and use the survey freely. The Chinese version of the instrument has been validated by the Mental Health Association Hong Kong (MHAHK). It is hypothesised that the intervention programme is efficacious in increasing the level of MHL of workers. A significant increase in the MHL score in the intervention group in comparison to the control group at the end of the intervention period will be able to demonstrate the efficacy of the intervention.

#### Secondary outcome measures

Secondary outcomes include burnout, stress, and health-related quality of life. These will be examined by the following different instruments.

Burnout will be evaluated by the Maslach Burnout Inventory (MBI), which is specifically designed to measure the extent of burnout in adults in the workplace [18]. The instrument consists of three main domains capturing three different aspects of the burnout phenomena in individuals: emotional exhaustion, depersonalisation, and personal accomplishment. Emotional exhaustion measures the feelings that the worker is emotionally exhausted by his/her work. Depersonalisation captures the state that the worker is impersonally responding to recipients of one’s service, care treatment, or instruction. Personal accomplishment measures the level of competence and successful achievement of the worker in providing services [18]. This instrument has been fully validated and has been widely used around the world for many years. It has been translated into many languages. Recent studies on the psychometric properties of the MBI suggested that the three-factor model fitted the data better than other alternative models with high internal consistency for all three subscales, yielding Cronbach’s α values of 0.84, 0.87, and 0.88, respectively [19].

Stress will be assessed by the Anxiety subscale of the Depression, Anxiety, and Stress scale (DASS) [20]. The DASS is a fully validated and commonly used instrument designed for the assessment of stress, depressive symptoms, and anxiety. This scale has good psychometric properties, which include strong reliability and validity for both the English and the Chinese versions [20, 21].

Health-related quality of life (HRQoL) as an indication of general health will be measured by the five-level version of the European Quality of Life-5 dimensions (EQ-5D-5L) [22]. The validity of the EQ-5D-5L has been well demonstrated and widely published (https://euroqol.org/eq-5d-instruments/eq-5d-5l-about/). A Chinese version of the EQ-5D-5L has also been validated and commonly used in many studies [23].

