### Statistical methods

#### Statistical analysis plan

The analysis of the primary and secondary outcome measures will be conducted in accordance with the study design as a wait-listed cluster randomised trial and the nature of the variables. An intention-to-treat analysis will be applied to all primary and secondary outcomes. Any missing data will be imputed using the multiple imputation by chained equations approach. Should there be any differences identified between the intervention arm and the wait-list controls by comparisons of the baseline data collected, these variables will be considered potential confounders to be adjusted. A significance level of 5% will be adopted for testing all hypotheses.

The primary outcome measure of the study, namely MHL, will be analysed using a repeated-measures approach with possible adjustments to participants’ and sites’ characteristics. This will involve comparison of the mean change in the MHL scores from baseline to the completion of the intervention programme between the intervention and control groups (i.e. from T0 to T1). Since the study is a cluster randomised trial, the cluster sampling effect will be adjusted for. In order to cater for the sampling technique as well as the repeated measures of the outcome variable, the generalised linear latent and mixed model (GLLAMM) will be applied to test for any group differences.

For secondary outcome measures, the variables are of the same nature as for the MHL, namely continuous variables, and thus the approach of analyses will be the same. For the follow-up data, since all participants will receive the intervention programme, there will not be a distinction between the intervention and control groups and thus all participants will be considered a single group. Hence, the analysis will only focus on the changes in outcome measures across time. For the repeated measures of the outcome variables, a linear mixed-effect model will be applied.

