## Discussion

This trial aims to evaluate the efficacy of a workplace mental well-being intervention programme that involves both the organisation and the individual components in meeting the mental health needs of workers. This intervention is a novel approach to occupational health in an area which is underserved by research and which is receiving increasing attention. An adequately powered RCT is required to confirm that this dual approach of an organisation environmental scan and evidence-based psychoeducation training in mental health literacy is efficacious in increasing the MHL, reducing burnout and stress, as well as enhancing the health-related quality of life of the participants. The proposed trial method, a wait-listed cluster randomised control trial, is considered appropriate in terms of the study design in providing adequate strength of evidence as well as the ethical consideration that the controls should also gain the benefits of the intervention.

If the trial results are in line with the hypothesis that supports the efficacy of the intervention programme, this will provide an evidence-based approach for an effective workplace mental well-being intervention programme that could not only enhance the understanding of mental health issues, but also reduce work-related burnout and stress as well as increase workers’ quality of life. This intervention is scalable as it adopts the e-Health and e-Learning approach and is formulated as blended training consisting of a series of self-paced online e-Learning modules. This will provide a flexible platform for all workplaces and workers can attempt these modules at their own convenience and at their own pace. Companies can be encouraged to incorporate the intervention programme into the staff development programme as well as the staff Occupational Health and Safety framework. Regular training can be provided by MHAHK to the staff body as well as the unit management through an agreeable partnership.

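### The secondary outcome stress is defined by the DASS Anxiety subscale, so the definition does not match the objective it serves

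*Protocol article*

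**What the plan says.** The Secondary objectives include improving workers' mental well-being, "particularly in the reduction of stress". The abstract's Methods paragraph says the trial will determine whether the programme is effective in "reducing burnout and stress scores, as measured by standardised and validated scales". The section Secondary outcome measures opens with the list: "Secondary outcomes include burnout, stress, and health-related quality of life".

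The same section then gives the only sentence that says how stress is measured: "Stress will be assessed by the Anxiety subscale of the Depression, Anxiety, and Stress scale (DASS) [20". The sentence after it describes the DASS as "designed for the assessment of stress, depressive symptoms, and anxiety".

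The Statistical analysis plan section names no subscale. It says: "For secondary outcome measures, the variables are of the same nature as for the MHL, namely continuous variables", and applies the same approach as for mental health literacy (MHL), which compares the mean change from T0 to T1 between arms. The Discussion again states the aim as "reducing burnout and stress, as well as enhancing the health-related quality of life of the participants".

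**The concern.** The outcome has one name and its measurement rule has another. An analyst or survey builder who follows the sentence will produce an anxiety score and put it in the results table under stress. A positive result would then support a claim that the data do not address. A null result would be read as no effect on stress when stress had not been scored.

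Stress is the stated emphasis of the well-being objective, and the Intervention section adds a training module on stress reduction and burnout prevention. The mismatch therefore falls on an effect that the programme is explicitly built to produce.

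**Working it through.** No arithmetic applies: the point does not depend on alpha, power, effect size, dropout or cluster size. The check is to compare every place in the article that names stress, anxiety or the DASS.

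**Where stress is the target**
- Abstract, Methods: stress scores, together with burnout.
- Secondary objectives: stress as the emphasis of the well-being objective.
- Secondary outcome measures, opening list: stress, beside burnout and health-related quality of life.
- Discussion: stress, beside burnout and quality of life.

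**Where its measurement is defined**
- Secondary outcome measures, one sentence: the Anxiety subscale of the DASS.

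**Where anxiety appears otherwise**
- In the Background, in a prevalence figure for mixed anxiety and depression disorders.
- In the name and description of the DASS. It is never an objective or an outcome.

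**Could another section supply the stress measure?**
- The Statistical analysis plan section only calls the secondary outcomes continuous. Its model would be applied to whichever score is collected.
- The Moos Work Environment Scale covers work pressure, but it belongs to the organisational scan, is collected at the briefing session and is not listed as an outcome.
- No sentence names the DASS Stress subscale or argues that anxiety can stand in for stress.

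**What follows if the sentence is applied literally**
1. The between-arm contrast labelled stress is the difference in T0 to T1 change on the Anxiety subscale.
2. The later analysis treats all participants as one group and follows change over time, so it would carry the same mislabelled score. The intervention arm is assessed at T0, T1 and T2; only the controls have T3.
3. The loss depends on what the online form contains, which the article does not state:
   - *Full DASS, or at least the Stress items, administered:* the stress score can still be derived. The harm is the wrong scoring definition.
   - *Anxiety items only administered:* no stress score exists at any wave. The baseline cannot be collected again once the programme has begun, so the T0 to T1 comparison of stress cannot be recovered.

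**What is untouched**
- The primary outcome is MHL, and efficacy is to be judged on it.
- The sample size (about 400 workers at 20 sites, effect size 0.5 standard deviations) is set on the MHL score alone. Changing the DASS subscale alters none of these figures.

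**The case against.** The strongest reply is that this is a slip of one word. Every other statement targets stress, the description of the DASS lists stress first, and the survey form and the schedule of measures (Fig. 2) are not visible. The survey may well contain the right items. This is fair, and it limits what can be claimed about harm. It does not make the sentence right: if the Stress subscale was meant, the definition is false; if the Anxiety subscale was meant, the outcome label and the objective are wrong. One of them needs correcting either way. Nor is this detail left to a fuller document, because the article names a subscale. If stress scores were later reported against this published definition, it could look like an undocumented change of outcome.

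A reader might infer more than the documents support:
- **That stress will certainly never be measured and the loss is irreparable.** This holds only if the Stress items are not administered, and the article does not say whether they are.
- **That one of the three secondary objectives cannot be answered at all.** That objective is mental well-being, with stress as its emphasis. An anxiety score would bear on part of it. What fails is the stress component and the label on the result.
- **That the wrong subscale is used at T0 to T3 for everyone.** T3 applies to controls only.
- **That the programme has no anxiety content, so an anxiety score is irrelevant to it.** The article names the added stress and burnout module but does not list the other Mental Health First Aid modules, so this cannot be shown.

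**Conclusion.** The definition of the stress outcome is wrong as written. The article separates stress from anxiety, promises an effect on stress in four places, and scores it with the Anxiety subscale without giving a reason. This conclusion rests on the article's text alone.

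Its reach is one secondary outcome, including that outcome's randomised T0 to T1 comparison. Its size ranges from a wrong scoring definition, if the Stress items are in the survey, to permanent loss of the stress data, if they are not. The documents do not settle which. The primary outcome, the primary analysis and the sample size stand. The correction deserves priority because of timing: the worse of the two cases can be prevented only before baseline data are collected.

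**What to change.** In Secondary outcome measures, change the defining sentence to name the DASS Stress subscale as the stress outcome. This is the reading to adopt because every objective names stress.

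Before recruitment opens, check that the online form includes the Stress items at each arm's scheduled assessments: T0, T1 and T2 in both arms, and T3 for the controls.

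If the Anxiety subscale was intended, or is kept alongside, list it as a separate anxiety outcome, report it under that name, and draw no conclusion about stress from it. Record the correction as a dated protocol modification, so that it is not later taken for outcome switching. The Study monitoring section already requires modifications to be reported to the Research Ethics Committee.

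The cost is one sentence, one check of the form and one report to the committee. No participants or visits are added; if the Stress items are missing, the survey gains those items. The article was published on 4 December 2019 and recruitment was due to begin on 1 January 2020, so on the stated dates the change could be made before baseline.
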